## Abstract

**Background:**

As the number of elderly and multimorbid patients increases, healthcare has become more complex. This requires good coordination of treatment and care given the various  health care professionals involved (e.g. general practitioners, medical specialists, physicians’ assistants). Lack of coordination jeopardizes seamless, evidence-based treatment and care, and eventually reduces clinical effectiveness. The aim of the study is a) to describe and explore information transfer and interprofessional collaboration in ambulatory cardiac care, b) to describe and explore the role of provider networks from the perspective of patients and providers, focusing on healthcare coordination and the uptake of recommended practices.

**Methods:**

Two related studies are planned: a) an observational study of healthcare provider networks, involving 600 patients with chronic (atherosclerosis-related) cardiovascular disease from 40 general practices and up to 320 healthcare providers (general practitioners, medical specialist, physicians’ assistants), and b) a qualitative interview study with up to 80 healthcare professionals and patients. Furthermore, we will analyse claims data of a large German health insurer to explore provider networks in ambulatory cardiac care.

**Discussion:**

The project aims to provide insight into factors, processes and mechanisms of information transfer and interprofessional collaboration, which affect seamless, evidence-based healthcare practice. This will contribute to the design of strategies for improving health care practice and to the development of measures of coordination for future research.

**Trial registration:**

We registered the study prospectively on 7 November 2019 at the German Clinical Trials Register (DRKS, www.drks.de) under ID no. DRKS00019219.

## Background

Health outcomes can only be optimized when recommended treatment and care are implemented comprehensively in healthcare practice, and unnecessary or unsafe practices are avoided. This can be enhanced by a variety of strategies, such as continuing medical education of healthcare professionals (HCP) and financial incentives for healthcare providers. Implementation strategies need to address the fact that increasing numbers of patients receive healthcare from a range of HCPs, simultaneously or consecutively, as a result of increasingly complex care needs and ongoing specialization of healthcare providers. These professionals have different backgrounds (in medicine, nursing and allied health professions) and are based in various healthcare organizations and sectors (e.g. ambulatory care, hospitals, rehabilitation centres). Their involvement in patient care may fluctuate over time; for instance, before, during and after hospital admission. In some settings, HCPs collaborate in structured teams, but such patient care teams (with regular meetings to share information and coordinate activities) are uncommon in ambulatory care and across primary and hospital care. Although several health professionals are usually involved in the care for a patient, they do not necessarily collaborate actively. In those situations, it is a challenge to achieve well-coordinated healthcare delivery; healthcare which is clinically coherent and logistically non-interrupted over time and across providers. Low coordination is associated with increased risks for patient safety [1], lowered patient activation [2], avoidable hospital admissions [3], and lowered patient experience of confidence and safety [4]. The German healthcare system is (like other modern healthcare systems) fragmented, and achieving better coordination of care is high on the health policy agenda [5].

Coordination of care is influenced by many factors. Firstly, shared ideas about what is desirable practice, such as shared multi-disciplinary clinical guidelines, enhance coordination across different healthcare providers. It is difficult to achieve well-coordinated care, if each healthcare profession and institution follows its own recommendations and these are conflicting with those of others. Secondly, coordination depends on effective cooperation between healthcare providers around individual patients and local populations. This requires adequate information exchange, constructive cooperation behaviours, and good relationships between patients and providers [6]. Cooperation work on a case-by-case basis is time consuming, so much of it takes the format of structured information transfer (e.g. referral letters of general practitioners to other medical specialists). HCPs’ attitudes and competencies influence their interprofessional cooperation. Third, a range of contextual and health system factors (financial, organisational, legal) are barriers or facilitators of well-coordinated care. For instance, if coordination implies additional workload or a financial loss, which is not compensated for, it is unrealistic to achieve improvement in practice.

The proposed study will explore the role of population structure [7], particularly emerging social networks of healthcare providers [8], on healthcare providers’ performance and patients’ experience of healthcare. For this purpose, we will apply social network analysis (SNA) to examine healthcare providers’ cooperation. The usefulness and feasibility of SNA methods were successfully tested in pilot studies [9–11]. The aim of the study is a) to describe and explore variation in information transfer and interprofessional collaboration in ambulatory cardiac care in Germany and b) to describe and explore the role of provider networks from the perspective of patients and providers, focusing on healthcare coordination and the uptake of recommended practices.

## Methods and design

The research project ‘ExKoCare’ is a multicentre, observational (non-interventional) study that uses a mixed-methods approach including a) a quantitative survey study, b) a qualitative interview study and c) a quantitative analysis of health insurance claims data.

### Quantitative survey study

#### Design and setting

Observational study in a stratified random sample of 40 general practitioners’ practices (GP practices) and surrounding cardiologists (approximately 5 per GP practice) with whom they are likely to collaborate regarding the targeted patient populations. The sample will involve practices from three different German states (Baden-Württemberg, Rhineland-Palatinate and Saarland). If the numbers allow for it, the sample will be stratified such that it adequately represents small and large practices, practices within and outside of organized practice networks, practices within and outside of GP-centred care (“Hausarztzentrierte Versorgung”), and practices in rural as well as urban areas. As these characteristics are not all available upfront (except for training practices), we will recruit a random sample and sample within strata to compose the stratified sample. For practical reasons, we intend to recruit within an area of maximum 200 km from Heidelberg.

#### Study population and sampling

From publicly available lists of the Statutory Health Insurance Agencies of Baden-Württemberg (KVBW), Rhineland-Palatinate (KVRLP) and Saarland (KV Saarland), primary care practices within designated administrative districts will be randomly drawn and invited to take part in the study until the target sample size has been reached.

To enhance the homogeneity of the study population, we will focus on patients with coronary heart disease (as indicator for atherosclerotic vascular disease) and at least one other chronic disease (chronic heart failure, diabetes mellitus, chronic obstructive pulmonary disease, chronic renal failure or depression). Within these conditions, we will select patients with moderate to high disease severity, using ICD-codes. Primary care practices will be asked to invite 15 patients for the study. Primary care physicians, respectively their assistants, will be asked to generate a list of patients potentially eligible for our study by using their practice’s documentation software. Patients need to have visited the practice within the past 3 months; patients with a short life expectancy or major cognitive limitations will not be approached. The practice generates a printed list and removes potential identifiers except ICD-codes. Afterwards, one member of the research team visits the practice and randomly chooses the desired number of patients from the list. Alternatively, instructions for randomized sample drawing are sent to the practice and staff members choose patients accordingly themselves. The practice is then provided with a sufficient number of blank envelopes and questionnaires through the research team and will send out questionnaires to the selected patients. The patient receives the questionnaire, is free to fill it out and send it back anonymously directly to the research institute. The study was powered to detect a small to medium effect size (*r* = 0.15) on the primary outcome. Power was set at 0.8, significance level at 0.05, and a design effect of 1.4 (40 clusters and an intraclass correlation coefficient of 0.01) was taken into account.

Ambulatory cardiologists will be contacted based on the geographical area they are based in. Depending on the location of the primary care practices in the study, cardiologists within a radius of about 25 km will be invited to take part in the study. They will be identified by publicly available data from the online database of the respective Statutory Health Insurance Agency.

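### The survey's 600 patients are the number invited, so the stated sample needs full return and the stated power needs about 81% return (about 63% on a more favourable reading)

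*Protocol article*

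**What the plan says.** The Methods part of the Abstract describes the survey as "involving 600 patients with chronic (atherosclerosis-related) cardiovascular disease from 40 general practices". Design and setting of the Quantitative survey study gives the same number of practices: "Observational study in a stratified random sample of 40 general practitioners’ practices (GP practices".

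Study population and sampling then describes how patients enter: "Primary care practices will be asked to invite 15 patients for the study". Supplies are described without a number: "The practice is then provided with a sufficient number of blank envelopes and questionnaires through the research team". Response is left to the patient: "The patient receives the questionnaire, is free to fill it out and send it back anonymously directly to the research institute".

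The same section closes with the power statement: "The study was powered to detect a small to medium effect size (*r* = 0.15) on the primary outcome", followed by power 0.8, significance level 0.05 and "a design effect of 1.4 (40 clusters and an intraclass correlation coefficient of 0.01) was taken into account". The statement gives no resulting sample size and no expected return.

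**The concern.** One number serves two purposes. In the Abstract, 600 is the number of patients in the study. In the sampling section it is the product of practices and invitations. The two agree only if every invited patient returns a usable questionnaire, and the described procedure makes return voluntary and anonymous.

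Nothing in that section closes the gap. The rule that recruitment continues until a target is met applies to the drawing of practices. No replacement draw of patients is described, and 15 is the only patient number given per practice.

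What is at stake is the stated size of the survey and, depending on the return, the power claimed for the primary outcome, patient-reported coordination of care.

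**Working it through.** **Inputs from the protocol article.** 40 practices; 15 invitations per practice; r = 0.15; power 0.8; alpha 0.05; design effect 1.4, attributed to 40 clusters and ICC 0.01.

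**Assumed, because the article does not say.** The test is two-sided. Return rates are illustrative.

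**Step 1: the stated 600.** 40 x 15 = 600, which is the number of invitations.

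**Step 2: the number that the power inputs need.** For a correlation, by Fisher's z:

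n = ((1.960 + 0.842) / atanh(0.15))² + 3 = (2.802 / 0.1511)² + 3 = 346.6, rounded up to 347.

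With the stated design effect: 347 x 1.4 = 485.8, rounded up to 486. The regression form of the formula gives 341, and 478 after inflation. A one-sided test gives 384 by Fisher's z. None of these is 600, so within the article 600 is explained only by 40 x 15.

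**Step 3: margin and break-even at design effect 1.4.** 600 - 486 = 114, and 114 / 600 = 19%. The return needed for 0.8 power is 486 / 600 = 81%. If all 600 came back, power would be 0.88.

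**Step 4: a more favourable design effect.** The figure 1.4 is close to 1 + (40 - 1) x 0.01 = 1.39, which uses the number of clusters where the formula takes the cluster size. With 15 per practice it is 1 + (15 - 1) x 0.01 = 1.14, and it falls further as fewer questionnaires return. With m returns per practice, 80% power requires 40m / (1 + (m - 1) x 0.01) to be about 347. This gives m = 9.4, or 376 returns, and 376 / 600 = 63%.

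**Step 5: power at assumed return rates.** Power = Phi(atanh(0.15) x sqrt(N / DE - 3) - 1.960), where N is the number returned and DE the design effect.

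| Assumed return | N returned | Power, DE 1.4 | DE with ICC 0.01 at realised cluster size | Power, that DE |
|---|---|---|---|---|
| 100% | 600 | 0.88 | 1.140 | 0.93 |
| 80% | 480 | 0.80 | 1.110 | 0.88 |
| 70% | 420 | 0.74 | 1.095 | 0.84 |
| 60% | 360 | 0.67 | 1.080 | 0.78 |
| 50% | 300 | 0.59 | 1.065 | 0.71 |

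Example, 60% and DE 1.4: 360 / 1.4 = 257.1; 0.1511 x sqrt(254.1) = 2.41; 2.41 - 1.96 = 0.45; Phi(0.45) = 0.67.

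**The case against.** The strongest reply is that an allowance exists in effect. The inputs need 486 and 600 are invited; 486 / 0.80 = 608, so 600 would fit a planned loss of roughly one fifth. A reader might infer from the article that non-response was ignored altogether. The documents do not support that: there is a 19% margin over the number needed. What stands against the reply is that the article never presents the margin as an allowance and calls all 600 patients involved in the study.

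A second reply is that this is a condensed article, and a return-rate assumption may stand in the full protocol. That is fair, and the absence of a rate is not the finding. The finding is that the article uses one number for both invited and included patients, which a rate given elsewhere would not repair.

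A third is that the supply of envelopes is left open, so more than 15 might be sent. The wording allows it, but it refers to the patients already selected and gives no figure beyond 15.

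A reader might also infer that the survey will be underpowered because postal returns usually fall below these thresholds. The documents give no return rate, so only the conditional statement holds. Likewise, eligibility does not require a cardiologist contact, and one might expect incomplete cardiology items. The article neither says how often this would happen nor how the score would then be formed, so nothing is built on it here.

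**Conclusion.** The point holds as a mismatch between stated and deliverable sample size. As described, the procedure yields 600 patients only at 100% return. The claimed 0.8 power needs about 486 returns (81%) at the article's own design effect, or about 376 (63%) with ICC 0.01 at the realised cluster size.

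These figures assume a two-sided test, a single correlation adjusted by a design effect, and equal returns across practices. A one-sided test at design effect 1.4 would lower the break-even to 384 / 600 = 64%.

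Severity is moderate. Phase 4 of the Data-analysis section calls the study explorative and accepts many tests without adjusting the significance level. A smaller return makes estimates less precise and the power statement too favourable. It does not, through this defect, invalidate the planned models.

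**What to change.** In the Abstract and in Study population and sampling, state that 600 is the number of patients invited. Add the expected number of analysable questionnaires, with the return rate behind it, and quote power at that number using a design effect that matches the expected returns per practice. The only cost is a less favourable stated figure.

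Inviting more patients is optional. At an assumed 60% return, 486 / 0.60 = 810 invitations, or 21 per practice, would restore the number needed at design effect 1.4. Whether practices have that many patients who meet the diagnosis, severity and recent-visit criteria is not shown, so this would have to be checked before it is promised.

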##### Phase 4. Exploration of network-related determinants of coordination (research objective 2)

Quantitative analysis is primarily focused on the hypotheses concerning network-related mechanisms of coordination, which are specified in the conceptual model.

The respective mechanisms will be examined in two steps:

Step 1: Construction of measures for each practice, calculated from the documented networks or directly from the questionnaires:
opinion leader: presence of a care provider within or outside of a general practice influencing opinions as reported by care providers. (polytomous variable). Additionally, self-perception as an opinion leader by care providers (based on questionnaire).central care provider: degree of the healthcare provider with the highest centrality in the network (count variable, calculated from network data).density of network: proportion of connections of all possible connections (variable with values between 0 and 1, calculated from network data).homogeneity: consistency of clinical attitude views and multiprofessional cooperation (E-I parameter, which has values between − 1 and + 1, calculated from network data).presence of case manager (dichotomous variable, based on questionnaire).network reciprocity: average proportion of network members which can be reached through mutually confirmed pathways (count variable, calculated from network data).perceived change in the network of referral and consultation to other care providers (5-point-likert-scale, based on questionnaire).

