Step 2: Analysis of impacts. Potential impact of each of the network characteristics together with patient-reported coordination of care will be examined. The measured and constructed network characteristics will be added to the patient-level data as potential predictors for the patient-reported coordination of care and aspects of cardiac care delivery. We will analyse the provider-reported cooperation networks and the patient-reported cooperation networks separately. Linear or logistic regression models will be applied with distributions and link functions as appropriate for the observed distributions (e.g. normal, binomial, Poisson). Random coefficient models will be used in order to take clustering of data into account (patients with practices). The influence of individual patient characteristics will be explored in further analyses. Although a large number of statistical tests will be applied, we use the conventional *p* < 0.05 as cut-off for significance given the explorative character of the study.

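### The planning inputs r = 0.15, ICC 0.01 and power 0.8 are mutually inconsistent for the practice-level network predictors that carry the main hypotheses

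*Protocol article*

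**What the plan says.** The sample-size text under Study population and sampling (Quantitative survey study) reads: "The study was powered to detect a small to medium effect size (*r* = 0.15) on the primary outcome". It continues: "Power was set at 0.8, significance level at 0.05". Clustering enters the calculation through the further statement that "a design effect of 1.4 (40 clusters and an intraclass correlation coefficient of 0.01) was taken into account". The text does not say whether r is a patient-level or practice-level correlation, whether the ICC is total or residual, or whether the test is one- or two-sided.

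The planned size is given in the Abstract as "involving 600 patients with chronic (atherosclerosis-related) cardiovascular disease from 40 general practices", and the sampling section adds: "Primary care practices will be asked to invite 15 patients for the study". So 40 x 15 = 600, which assumes that every invited patient responds. No response rate is stated.

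Phase 4 of the data analysis directs the quantitative work mainly at the hypotheses about network mechanisms. Its first step is described as "Construction of measures for each practice, calculated from the documented networks or directly from the questionnaires". In the second step, "The measured and constructed network characteristics will be added to the patient-level data as potential predictors for the patient-reported coordination of care". Random coefficient models account for patients clustered in practices. The influence of individual patient characteristics is left to further analyses.

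**The concern.** Density, degree of the most central provider, homogeneity, reciprocity, presence of a case manager and the other Step 1 measures are constant for all patients of a practice. They can explain differences between practices but none of the differences between patients of the same practice. The ICC is the share of outcome variance that lies between practices, so it caps what any such predictor can explain. The plan sets that share at 1% and at the same time powers for an effect that explains 2.25% of the variance (0.15 squared).

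What is at stake is how the results will be read. A non-significant network effect on the primary outcome would be interpreted against a claimed power of 0.8. Under the plan's own ICC, the largest effect that could exist would be detected with clearly lower probability.

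**Working it through.** **Inputs.** r = 0.15, power 0.8, alpha 0.05, ICC 0.01, design effect 1.4 and 40 clusters (Study population and sampling); 600 patients (Abstract); 15 patients invited per practice (Study population and sampling); one predictor value per practice (Phase 4, Step 1); patient-level outcome (Phase 4, Step 2). Two-sided testing is assumed unless noted.

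**1. The plan's own figure.** For a simple correlation, n = ((z_alpha + z_power) / atanh(r))^2 + 3 = (2.8016 / atanh(0.15))^2 + 3 = 346.6, so 347. Multiplied by 1.4 this is 486 (one-sided: 274 x 1.4 = 384). Neither is 600, although 486 of 600 would fit an unstated response of about 81%. With 600 / 1.4 = 429 effective patients, power at r = 0.15 is 0.88. The calculation therefore looks like one for an ordinary patient-level correlation inflated by a design effect.

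**2. The design effect.** The usual formula is 1 + (m - 1) x ICC, with m the number of patients per cluster.
- m = 15: 1 + 14 x 0.01 = 1.14.
- With 40 in place of m: 1 + 39 x 0.01 = 1.39, which rounds to the stated 1.4.

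The stated value thus appears to use the number of practices where the cluster size belongs. This is a separate slip; correcting it does not move the ceiling below.

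**3. The ceiling.** Write the outcome, scaled to variance 1, as Y = u + e, with practice effect u (variance ICC) and within-practice residual e. For a predictor X that is constant within a practice:

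corr(X, Y) = corr(X, u) x sqrt(ICC) <= sqrt(ICC) = sqrt(0.01) = 0.10.

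Reaching r = 0.15 needs ICC >= 0.15^2 = 0.0225, which is 2.25 times the stated value.

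**4. Power at the ceiling (total ICC 0.01, 40 x 15, full response).**
- Regression of practice means on 38 df, simulated: 0.65 two-sided (0.67 by non-central t); about 0.76 one-sided (up to 0.78).
- Fisher approximation with design effect 1, the most favourable case because the predictor then absorbs all practice variance: 0.69 two-sided, 0.79 one-sided.
- Smallest r with 80% two-sided power at 600 patients and design effect 1: 0.114, already above 0.10.
- If the predictor explains only half of the practice variance (r = 0.071): about 0.36.

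None of these reaches 0.8, one- or two-sided.

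**5. Readings under which r = 0.15 is attainable.**
- *0.01 is the residual ICC.* Total ICC = 0.0225 + 0.9775 x 0.01 = 0.0323. Simulated power with 600 returns is 0.90. Share of practice variance explained: 0.0225 / 0.0323 = 0.70, a practice-level correlation of 0.15 / sqrt(0.0323) = 0.83.
- *1.4 is right and the ICC is not.* With 15 per practice, ICC = 0.4 / 14 = 0.0286, the ceiling is 0.169 and simulated power at r = 0.15 is 0.91. Share explained: 0.0225 / 0.0286 = 0.79. This contradicts the stated 0.01.

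**6. Sensitivity of r = 0.15 to the total ICC (ICCs are assumptions; 600 returns, two-sided).**

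| Total ICC | Share of practice variance explained | Power |
|---|---|---|
| 0.01 | not attainable | - |
| 0.032 | 70% | 0.90 |
| 0.05 | 45% | 0.84 |
| 0.10 | 22.5% | 0.68 |

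**The case against.** The strongest reply is that the ceiling depends on how two unqualified figures are read. The article does not call 0.01 a total ICC, and the residual ICC is what enters the design effect of a regression coefficient. On that reading r = 0.15 is attainable with power of about 0.90. This stands as a possible reading, but it makes the effect a demanding one: a single characteristic must explain about 70% of everything that differs between practices, which sits badly with calling it small to medium. The plain reading of an unqualified ICC is the total.

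It can also be said that the power sentence never ties r to a practice-level predictor, and that the ceiling does not apply to patient-level covariates or to correlations between practice means. That is true. But patient characteristics are deferred to further analyses, and the outcome is modelled on patient-level data. If r referred to either of those, the power statement would not cover the analysis that carries the main hypotheses.

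Finally, the study calls itself exploratory and uses an unadjusted 0.05 cut-off for that reason. This lowers the severity. It does not reconcile the figures, and the Discussion still presents the project as testing hypotheses.

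Two stronger conclusions are tempting and are not supported. A reader might infer that r = 0.15 can never occur in this design. That holds only for a total ICC below 0.0225, and 0.01 is a planning assumption, not a measured property of the population. A reader might also infer that a null result would be inevitable. With about 0.65 power at r = 0.10, an effect at the ceiling would be found roughly two times in three.

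**Conclusion.** The point holds as an inconsistency between planning inputs. With 0.01 taken as the total ICC, a practice-level predictor cannot correlate with patient-reported coordination above 0.10. At that ceiling, 600 patients in 40 practices give about 0.65 two-sided power, or about 0.76 one-sided. The stated combination of r = 0.15, ICC 0.01 and power 0.8 therefore cannot describe the main hypotheses. It becomes coherent only if the total ICC is at least 0.0225, for example about 0.032 under a residual reading, where power is about 0.90.

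The conclusion assumes one predictor tested at a time, equal practice sizes and full response; fewer returns would lower these power figures. It does not show that the study is unable to detect network effects. The paragraph should be corrected, but the matter is not critical, because the study is described as exploratory.

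**What to change.** Restate the power paragraph for a practice-level predictor and give:
- the level at which r is defined;
- whether the ICC is total or residual;
- whether the test is one- or two-sided;
- the share of between-practice variance the predictor is assumed to explain;
- a design effect computed from patients per practice (1.14 at ICC 0.01 with 15 patients, not 1.4);
- the resulting power on about 38 degrees of freedom over a range of total ICCs, labelled as assumptions because the article supplies only 0.01.

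Add a sentence saying that at a total ICC of 0.01 no practice-level effect above r = 0.10 can arise, and that with 600 patients power then does not reach 0.8. If a response rate was assumed, state it and base the power on expected returns.

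The cost is rewording and a short recalculation. No additional patients or practices are needed. Depending on the ICC chosen, the restated power may come out above or below 0.8.

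### The stated design effect of 1.4 does not follow from an ICC of 0.01 with 15 patients per practice, which gives 1.14; the inputs of the power statement contradict each other

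*Protocol article*

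**What the plan says.** The power statement is in the protocol article, Quantitative survey study, Study population and sampling. It reads "The study was powered to detect a small to medium effect size (*r* = 0.15) on the primary outcome", then "Power was set at 0.8, significance level at 0.05", and adds that "a design effect of 1.4 (40 clusters and an intraclass correlation coefficient of 0.01) was taken into account". It does not print a required number of patients, before or after inflation, and it does not say whether the test is one- or two-sided.

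The same section gives the number of patients per practice: "Primary care practices will be asked to invite 15 patients for the study". The Methods part of the abstract describes a study "involving 600 patients with chronic (atherosclerosis-related) cardiovascular disease from 40 general practices", which matches 40 × 15 = 600. Design and setting also gives 40 as the number of practices. Phase 4 of the data analysis treats patients as clustered within practices and handles this with random coefficient models.

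**The concern.** A design effect for clustering is a function of the ICC and the cluster size. The number of clusters does not enter it. Yet the parenthesis explains the 1.4 by the number of practices and the ICC, and leaves out the patients per practice. Read with the rest of the section, 40 is the number of clusters and 15 the cluster size, and these do not yield 1.4 at an ICC of 0.01.

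This sentence is the only justification of sample size for the primary outcome. Because no required number is printed, a reader can only rebuild it from these inputs, and the inputs disagree. The ICC matters here because most of the network characteristics in Phase 4 are built for each practice and then attached to patient records. Such a predictor is constant within a practice, so the full design effect applies to it. The 600 patients are also people invited to return a questionnaire voluntarily, so the response rate that would be adequate depends on which of the two figures is right.

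**Working it through.** **Inputs.** From Study population and sampling: r = 0.15, power 0.8, significance level 0.05, design effect (DE) 1.4, ICC 0.01, 15 patients invited per practice. From the abstract and Design and setting: 40 practices; from the abstract: 600 patients. Assumption: a two-sided test, since sidedness is not stated.

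**1. Trying to reproduce 1.4.** DE = 1 + (m − 1) × ICC, with m the number of patients per practice.

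| Reading | Calculation | DE |
|---|---|---|
| Stated cluster size and ICC | 1 + 14 × 0.01 | 1.14 |
| 40 used as cluster size | 1 + 39 × 0.01 | 1.39 |
| 40 used without subtracting 1 | 1 + 40 × 0.01 | 1.40 |
| m = 15, ICC 0.03 | 1 + 14 × 0.03 | 1.42 |

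Read backwards, a DE of 1.4 at ICC 0.01 needs m = 0.4/0.01 + 1 = 41 patients per practice, which no section supports. At m = 15 it needs ICC = 0.4/14 ≈ 0.029.

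Unequal cluster sizes do not explain it. With DE = 1 + ((1 + CV²) × m − 1) × ICC, m = 15, ICC 0.01 and a coefficient of variation as large as 1.0, DE = 1 + (2 × 15 − 1) × 0.01 = 1.29.

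**2. Number needed without clustering.** By Fisher's z: ((1.960 + 0.842)/atanh(0.15))² + 3 = 346.6, so 347. A one-sided test would give 274.

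**3. Power if all 600 are analysed (r = 0.15, two-sided).**
- DE 1.14: effective n = 600/1.14 = 526, power about 93%.
- DE 1.4: effective n = 600/1.4 = 429, power about 88%.

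**4. Returned questionnaires needed from 40 practices.** When some patients do not respond, m falls and so does DE. Both must therefore be solved together: 40m / (1 + (m − 1) × ICC) = 347, which gives m = 347 × (1 − ICC) / (40 − 347 × ICC).
- ICC 0.01: m = 343.53/36.53 = 9.40 and 40m = 376.2, so about 377 returned (63% of 600). DE at that size is about 1.08.
- ICC 0.029 (0.4/14): m = 11.20 and 40m = 448.2, so about 449 returned (75% of 600). DE at that size is about 1.29.

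**The case against.** The strongest reply is that nothing in the study turns on this figure. At the stated ICC, 1.4 asks for more patients than 1.14 does, so the error is on the safe side. With 600 analysed, power is above 0.8 under either value. The analysis models clustering directly and will estimate it from the data, and Phase 4 calls the study explorative. All of this stands. It bears on how serious the point is, not on whether the sentence is correct.

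It is also fair to say that the cause is not established. The parenthesis naming the 40 practices makes confusion of cluster count with cluster size plausible. But an ICC of 0.03 printed as 0.01, or 1.14 printed as 1.4, would leave the same text, and the underlying calculation could then have been sound.

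Two stronger readings are tempting, and the documents support neither:
- **The study is underpowered.** At ICC 0.01 and a two-sided test, power falls below 0.8 only if fewer than about 377 of the 600 questionnaires are returned, and no response rate is given.
- **The required sample was overstated by 23%.** That compares 347 × 1.4 = 486 with 347 × 1.14 = 396. Neither number is in the article, both assume a two-sided test, and 486 does not equal the planned 600. They also hold m at 15, whereas 396 or 486 analysed patients from 40 practices would mean 9.9 or 12.15 per practice.

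**Conclusion.** The point holds as an error in the power statement. The stated design effect of 1.4 cannot be obtained from an ICC of 0.01 and 15 patients per practice; those give 1.14, and no other cluster size in the article rescues it. Either the design effect or the ICC is wrong as printed, and the article does not show which.

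The practical effect is limited. If ICC 0.01 was intended, the error is conservative. What remains open is the number of returned questionnaires that supports the stated power: about 377 or about 449, a gap of 72. A response of, say, 68% (408 returned) would be enough under the first figure and short under the second. These numbers rest on a two-sided test, 40 practices of equal size and r = 0.15.

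**What to change.** Rewrite the one sentence so that the ICC, the cluster size and the design effect agree. Take the cluster size as the expected number of analysed (returned) questionnaires per practice rather than the 15 invited. State the sidedness of the test, the expected response and the resulting required number of patients.

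The sponsor must say which ICC was intended and on what grounds. It should not be back-solved from 1.4, since that figure may itself be the mistake. If ICC 0.01 is confirmed, the required number is about 377 returned questionnaires; if the intended value is about 0.029, it is about 449 (both two-sided, 40 practices).

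The cost is one corrected sentence. Recruitment and the analysis stay as they are.
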